**Methods/Design:**

The Family Options study will determine whether a manualized family based intervention designed to target both individual and family based factors in adolescent depression (BEST MOOD) will be more effective in reducing unipolar depressive disorders than an active (standard practice) control condition consisting of a parenting group using supportive techniques (PAST). The study is a multicenter effectiveness randomized controlled trial. Both interventions are delivered in group format over eight weekly sessions, of two hours per session. We will recruit 160 adolescents (12 to 18 years old) and their families, randomized equally to each treatment condition. Participants will be assessed at baseline, eight weeks and 20 weeks. Assessment of eligibility and primary outcome will be conducted using the KID-SCID structured clinical interview via adolescent and parent self-report. Assessments of family mental health, functioning and therapeutic processes will also be conducted. Data will be analyzed using Multilevel Mixed Modeling accounting for time x treatment effects and random effects for group and family characteristics. This trial is currently recruiting. Challenges in design and implementation to-date are discussed. These include diagnosis and differential diagnosis of mental disorders in the context of adolescent development, non-compliance of adolescents with requirements of assessment, questionnaire completion and treatment attendance, breaking randomization, and measuring the complexity of change in the context of a family-based intervention.

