### Aims and hypotheses

The primary aim of the trial is to evaluate the efficacy of the two interventions as: (a) treatments for youth mental health problems and (b) as methods of engaging youth in treatments. The secondary aims will include: (c) to build capacity and increase service integration across several service delivery sectors by providing evidence based intervention programs for youth and their families; (d) to influence national and state government policy on the use of family based approaches in the field of youth mental health; and (e) make use of the study partnerships for national promotion and dissemination of family-based treatment models for youth mental health.

The primary study hypothesis is that youth in the BEST MOOD intervention will demonstrate significantly greater rates of remission of depressive disorders (major, minor, or dysthymia), than youth in the PAST intervention. Secondary hypotheses include: (a) that parental and youth mental health and relationships will improve in response to both interventions, but significantly more so in response to BEST MOOD; (b) that greater treatment engagement for youth will be associated with greater improvements in youth mental health outcomes; and (c) that youth in the BEST MOOD condition will report greater treatment engagement than youth in the PAST condition.

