### Parenting Adolescents Support Training (PAST)

The PAST intervention will act as the treatment-as-usual control condition in this trial. Parents will attend a professionally facilitated parenting group which uses supportive counselling techniques. The PAST intervention runs for eight, weekly two-hour sessions. Youth and siblings (aged 12 and over) are invited to join in the fifth week. This intervention has been manualized for the purpose of this study. The content of PAST has been designed to equate with standard practices in currently available services in Australia, where if any service is offered, it is likely to consist of a parent support group. The development of this intervention was guided by the current protocols for the family mental health support services in Victoria, Australia. The PAST intervention offers: (a) supportive counselling to assist parents to articulate and identify concerns and (b) psycho-education to increase parents’ knowledge about youth mental health problems. The main content of the PAST group is support and the opportunity to share experiences and ideas as well as receiving contact with a mental health professional.

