### Statistical analysis plan

Repeated measures binomial data will be analyzed over three time points using a binary logistic regression within the Generalized Linear Mixed Model (GLMM). The model will be fitted in STATA (xtmelogit). For any continuous-scale data we will use a linear mixed model approach in STATA. For both types of data we will explore variance-covariance structures for the evaluations within an individual. Clinical significance and an index of reliable change will be calculated for each measure using the criteria of Jacobson and Truax [46]. Findings will be analyzed in terms of standardized mean differences and effect sizes achieved will be compared to existing high quality trials to determine relative efficacy of this intervention. Multivariable multilevel models will also explore other covariates on the relationship between treatment arm and study outcomes, with a view to improving the intervention and specifying its ideal target population. Data will be stored in a locked cabinet, and a password protected computer file will contain de-identified (coded) data. A proportion of the data will be double-entered, and range checks will be performed for accuracy checking. Intention-to-treat analysis will be used with the last observation carried forward as a conservative estimate of outcome when data are missing at follow-up.

In addition, analysis of qualitative data from the transcribed interviews of participants who did not take up the option of treatment following intake/assessment, discontinued treatment, or completed treatment will be undertaken. Thematic analysis of participants’ accounts of their experience of the intake/assessment process and reasons for either engaging with or distancing themselves from the treatment offered will be undertaken. Meanings participants assign to the process will also be extracted from the data. Analysis of the data relevant to the phenomena of interest will assist in the identification of barriers to engagement and change for families.

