In terms of study design, we have been mindful of the challenges inherent in randomizing to treatments that use different modalities. One of the challenges in the field of adolescent mental health mentioned in the introduction is that the bulk of the existing evidence is based on individual adolescent psychological therapies, primarily CBT. In our previous attempt to conduct a head-to-head comparative trial of CBT versus BEST Plus, we found that parents randomized to the CBT condition whose adolescents refused to attend were strongly inclined to break the randomization and seek attendance to the BEST Plus condition. To address that issue, in this trial we offered equivalent group interventions for parents. While this has improved the problems of breaking randomization, it has also resulted in challenges in terms of obtaining adequate numbers to commence groups as scheduled.

Finally, the current trial of a family based intervention is based on a systemic model of therapeutic change. The measurement of outcomes needs to consider changes both in parents and in adolescents, and in terms of overall family dynamics. This is a more complex set of outcomes than one would find in a trial of an individual psychological therapy and is reflected in the set of measures of both outcomes and processes chosen in the trial.

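### A cross-trial comparison of effect sizes is said to determine BEST MOOD's relative efficacy, which a trial randomizing only against PAST cannot do

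*Protocol article*

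**What the plan says.** The Statistical analysis plan section names the metric, "Findings will be analyzed in terms of standardized mean differences", and in the same sentence says what it will be used for: "effect sizes achieved will be compared to existing high quality trials to determine relative efficacy of this intervention". It does not say whether the standardized difference is between arms or before-to-after. Between arms is the natural reading.

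The comparator is described in several places:

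- The abstract calls PAST an active control that represents standard practice.
- The PAST section says "The PAST intervention will act as the treatment-as-usual control condition in this trial" and also "The PAST intervention runs for eight, weekly two-hour sessions", the same length as BEST MOOD. PAST is manualized and professionally facilitated, and young people are invited from week five.
- Secondary hypothesis (a) under Aims and hypotheses expects "that parental and youth mental health and relationships will improve in response to both interventions, but significantly more so in response to BEST MOOD".

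The Discussion observes that "the bulk of the existing evidence is based on individual adolescent psychological therapies, primarily CBT". It reports that an earlier head-to-head trial against CBT was troubled by families leaving their allocated arm, and then says: "To address that issue, in this trial we offered equivalent group interventions for parents". This trial therefore has no CBT arm and no arm other than BEST MOOD and PAST.

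**The concern.** Citing other trials to put a result in context is ordinary practice. This sentence goes further. It sits in the analysis plan and presents relative efficacy as something the comparison will establish. The trial's own effect size answers one question: how much better is BEST MOOD than PAST? A published effect size answers the same kind of question about another treatment and another control. Subtracting or ranking the two mixes treatment effect with control strength, the spread of scores in each sample, and chance.

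If the sentence is followed, the trial report could state that BEST MOOD is more or less effective than other treatments, and no randomized comparison would stand behind that statement.

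**Working it through.** **1. Inputs.** From Sample size and power: d = 0.63, 57 analysed per arm (114 in total), 80 recruited per arm, two-sided alpha 0.05, power 0.90, therapy-group ICC 0.17 for the main outcome and 0.07 for continuous secondary outcomes, and 10% of variation explained by other model variables. Therapy-group size is not stated, so every group size below is an assumption.

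**2. The plan's figure of 57.** Without clustering, n per arm = 2 × ((1.960 + 1.282)/0.63)² = 52.9, or 53. Multiplying by the design effect 1 + (m − 1) × 0.17 and by 0.90 gives 56 for m = 2 and 72 for m = 4. As m is not given, 57 can be neither confirmed nor refuted. The point does not depend on it; 57 is used here only as the planned analysed number.

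**3. Precision of this trial's effect size.** SE(d) = √(2/n + d²/(4n)).

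- n = 57, no clustering: √(2/57 + 0.63²/228) = √(0.03509 + 0.00174) = 0.192. Half-width 1.96 × 0.192 = 0.38; interval 0.25 to 1.01.
- n = 80, no clustering: SE 0.162, half-width 0.32; interval 0.31 to 0.95.

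Clustering divides n by the design effect, so the half-width grows by the square root of that effect. At 57 per arm:

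| ICC | Assumed group size | Design effect | 95% half-width |
|---|---|---|---|
| 0.17 | 2 | 1.17 | 0.376 × √1.17 = 0.41 |
| 0.17 | 6 | 1.85 | 0.376 × √1.85 = 0.51 |
| 0.17 | 8 | 2.19 | 0.376 × √2.19 = 0.56 |
| 0.07 | 6 | 1.35 | 0.376 × √1.35 = 0.44 |
| 0.07 | 8 | 1.49 | 0.376 × √1.49 = 0.46 |

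**4. Chance in a two-trial comparison.** Suppose a second trial also has 57 per arm and the same true d of 0.63 (assumption), ignoring clustering. The SE of the difference between the two estimates is √2 × 0.192 = 0.271, a 95% range of ±0.53. The estimates differ by more than 0.2 with probability 2 × (1 − Φ(0.2/0.271)) = 46%, and by more than 0.3 with probability 27%, although the true effects are identical.

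**5. The comparator.** Let a treatment's own gain be 1.0 SD (assumption, for illustration). Its between-arm d is 1.0 minus the control's gain: 1.0, 0.8, 0.6 or 0.4 when the control gains 0, 0.2, 0.4 or 0.6 SD. One treatment takes four different places in a ranking through its control alone. The plan expects PAST families to improve, so the control's gain is not expected to be zero here.

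**6. Does the text limit the comparison?** Nothing in the article restricts it to trials with a PAST-like control, requires a shared comparator, or calls it descriptive.

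**The case against.** The strongest reply is that this is one clause in a condensed article. It contains no ranking rule or test, and nothing in it rules out confidence intervals or matching on comparator. Such detail may be in a full analysis plan. That stands as far as missing method goes, and the point does not rest on it. What the article does state is the inference, and no choice of interval or margin lets unanchored effect sizes establish relative efficacy.

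The reply is also right about direction. A reader might infer that an equally effective BEST MOOD would usually look weaker than existing therapies because PAST is a strong control. For example, with an assumed SE of 0.20 for the external trial, the SE of the difference is √(0.192² + 0.20²) = 0.277. If PAST exceeded the external control by 0.2, 0.3 or 0.5 SD, BEST MOOD would look worse in 76%, 86% or 96% of cases. The documents do not support that reading. The offsets are assumptions, the benchmark trials are not named, and the percentages only restate the offsets. The one external set used elsewhere for effect sizes, in Sample size and power, is family-based interventions against treatment as usual, and PAST is itself labelled treatment as usual. The Discussion's remark on CBT shows a difference in modality. It does not show other populations or outcomes, and it does not identify CBT trials as the benchmark.

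Finally, relative efficacy against outside treatments is neither an aim nor a hypothesis, and the aims on policy and dissemination do not mention it. That limits the weight of the point but does not remove the sentence.

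**Conclusion.** The concern holds as a flaw of interpretation in a secondary part of the plan. The design supports a conclusion about BEST MOOD versus PAST. It does not support one about BEST MOOD relative to treatments studied in other trials, and the sentence promises the latter. The reasoning is logical and needs no figure. The size of the chance component is a 95% half-width of about 0.38 for d = 0.63 at 57 per arm ignoring clustering, and about 0.41 to 0.56 at ICC 0.17 with two to eight per group (group sizes assumed). The direction of any bias cannot be stated from the documents.

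The primary hypothesis, its analysis and the sample size are untouched. If the effect size were meant as a before-to-after change, it would be even less comparable across trials.

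**What to change.** Replace the clause on determining relative efficacy with text such as:

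> Conclusions on efficacy rest on the randomized comparison of BEST MOOD with PAST. Between-arm effect sizes are reported with 95% confidence intervals that account for clustering by therapy group. Published trials are shown as descriptive context only, each with its comparator type. Any indirect comparison is limited to trials with a similar control and is labelled exploratory.

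This changes one sentence and needs no new data, analysis model or sample size. Its cost is that the trial gives up a relative-efficacy claim that its design cannot support.

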## Methods/Design

### Overview

The study is a multi-center, double-blind, randomized controlled trial comparing two group interventions: the BEST MOOD program and a treatment-as-usual supportive parenting program known as Parenting Adolescents Support Training (PAST). Both interventions are for families of youth who present with a unipolar mood disorder, here defined as major or minor adolescent depression or dysthymia. In both treatment conditions, families receive eight sessions of treatment delivered over two hours per week. The trial will run across several sites in both metropolitan Melbourne and the regional Victorian city of Geelong. Families will be recruited primarily from the intake service of a large government run mental health service in the eastern region of Melbourne (Eastern Health’s Child and Youth Mental Health Service; CYMHS), but community referrals will also be accepted from schools and community based health and mental health services, and via promotion of the study at community forums. At the completion of the interventions, face-to-face interviews will be conducted to better understand the level of engagement of participants with the treatment following intake/assessment. The aims of the qualitative component of the study are to explore the phenomena of not taking-up treatment, discontinuing treatment after commencement, completing treatment and benefiting from treatment, and the perceived influencing factors on these outcomes.

The primary outcome measure will be rates of remission of depressive disorder (major, minor, or dysthymia), according to a structured diagnostic clinical assessment, utilizing modules from the Structured Clinical Interview for *DSM-IV Childhood Diagnoses* KID-SCID; [28]. The secondary outcome measures will include: adolescent mental health (parent and self-reported), parent mental health, the young person’s level of engagement with mental health services, the parent-child relationship, and the therapist-client working alliance. Psychologists, social workers, and postgraduate psychology students who will be trained and supervised in one of the interventions for an equivalent amount of time, will deliver treatment. Therapists and assessors are blinded to the content of the alternate intervention, and are blinded to whether they are delivering the experimental or control condition in the study.

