### Eligibility criteria

#### Inclusion criteria

Families will be included in the study where there is an adolescent aged 12 to 18 years who is currently presenting with a depressive disorder. Specifically, the young person must, at the time of assessment, meet the criteria for either major depressive disorder, minor depressive disorder, or dysthymic disorder as assessed via current *DSM-IV* criteria.

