### Assessments and outcome measures

The following measures will be administered to assess the previously described study hypotheses across three time points during the trial: enrollment in the trial (T1), completion of treatment (T2), and three months post-treatment completion (T3). To maximize the clinical validity of the outcome evaluations, these assessments will involve both clinician administered and self-report measures. These measures have been chosen based on piloting in previous trials and in terms of minimizing participant burden while maximizing sensitivity to clinical change across key domains.

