### Sample size and power

The trial aims to recruit a total of *n* = 160 participants. Based on pilot work and previously conducted clinical trials of family-based interventions compared to treatment-as-usual conditions, it has been estimated that it is possible to generate an effect size of *d* = 0.63 in reduction of mental health symptoms, which is equivalent to 14% increase in the odds of remission [45]. Out pilot data also indicates that treatment type by time interaction is able to produce up to 50% remission in depression diagnosis, over and above treatment type. With an alpha of 0.05 and power level of 0.90 for two-tailed tests, intraclass correlation coefficient (ICC) of 0.17 for within therapy group variation (estimated from our pilot data), and estimated 10% of variation in the main outcome accounted for by other variables in the model (treatment arm, time, parental socioeconomic status), the minimum sample size required equates to *n* = 57 per treatment arm. Based on pilot studies, an attrition rate of 20 to 25% is anticipated. Therefore, a minimum of 80 participants into each of the two treatment conditions will be recruited. Comparisons will be undertaken between those who drop out and those who are retained in order to assess for attrition bias.

With respect to our secondary hypotheses, anticipated final sample size of 114 individuals, will also allow us to detect small effect size (d = 0.23) for the treatment arm by time interaction for continuous outcomes, with 90% power and alpha level of 0.05, assuming ICC of 0.20 for within-person (between-assessment) and ICC of 0.07 for within therapy group variation (estimated from our pilot data).

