## Discussion

There are many challenges in conducting clinical trials in adolescent mental health. These include diagnosis and differential diagnosis of mental disorders in the context of adolescent development, non-compliance of adolescents with requirements of assessment, questionnaire completion and treatment attendance, breaking randomization, and measuring the complexity of change in the context of a family-based intervention.

To assess the trial outcomes in the most convincing manner the research team opted to diagnose depression in adolescents using a structured interview to ensure that diagnostic criteria are met. This increases demand on participants and requires extensive training of the assessment team, as well as monitoring of the quality of such assessments. In the context of adolescent depression, the use of structured clinical assessments can be challenging since this is perceived as an onerous task by adolescents who often are not forthcoming about their mental health symptoms. Operationalizing outcomes on the KID-SCID as the primary outcome of the clinical trial is therefore not without risk; these include challenges of high attrition and missing data as well as the challenge of recruiting adolescents willing to undertake such assessments. To mitigate these risks, we developed a parent proxy version of the KID-SCID which will be administered to a primary caregiver, and we plan to assess its accuracy compared with the youth report version.

Another notable feature of our early experiences in setting up this trial has been the relatively high rate of initial reports of psychotic-like experiences within a cohort of depressed adolescents completing the KID-SCID. Upon further clinical assessment these experiences often do not meet full criteria for psychotic disorders, and are often fleeting experiences or experiences which are phenomenologically distinct from psychotic symptoms.

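### Last observation carried forward is called conservative, but for a remission outcome in youth who are all depressed at entry it is not so in general: if loss differs by arm, the bias can go either way

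*Protocol article*

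**What the plan says.** The missing-data rule stands in the protocol article under Statistical analysis plan: "Intention-to-treat analysis will be used with the last observation carried forward as a conservative estimate of outcome when data are missing at follow-up". The same section specifies a logistic mixed model for binary outcomes over three time points and a linear mixed model for continuous ones.

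The primary outcome (Overview) is remission of depressive disorder on a structured diagnostic interview. Under Inclusion criteria, "the young person must, at the time of assessment, meet the criteria for either major depressive disorder, minor depressive disorder, or dysthymic disorder", so the baseline value is the same for everyone. Assessments and outcome measures sets the times: enrolment (T1), end of treatment (T2) and three months after treatment (T3).

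On the amount of missing data, Sample size and power says that "an attrition rate of 20 to 25% is anticipated", with no figure by arm. The Discussion names "challenges of high attrition and missing data" among the risks of using the diagnostic interview as primary outcome.

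**The concern.** A rule that is conservative should not create a treatment difference where there is none. Here the carried value is not neutral. A youth lost before T2 is carried forward from T1 and counted as not remitted. A youth remitted at T2 and then lost is counted as remitted at T3, so relapse cannot appear. The remission rate in each arm therefore depends partly on how many were lost and when. If loss is unequal, part of the between-arm difference is a difference in retention.

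The rule also fits poorly with the chosen model. A mixed model can use incomplete repeated assessments directly. Copied values enter it as if they had been observed, although the plan also intends to explore the within-person covariance structure that copying distorts.

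**Working it through.** The article reports no figure for the effect of this rule, so there is none to reproduce.

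**Inputs from the article:** 80 randomised per arm, two-sided alpha 0.05, attrition 20 to 25% overall, all youth depressed at T1.

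**Assumptions:** the split of dropout by arm; true remission of 30 to 70% in both arms (the article's only remission figure is up to 50%, from pilot data); dropouts remit like completers; therapy-group clustering ignored. The test is a two-sided pooled z-test of two proportions by exact binomial enumeration, not the planned mixed model.

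**Step 1. Loss before T2, no true effect.** Carried-forward remission = true remission x (1 - dropout). False difference = remission rate among those lost x difference in dropout. Example with 40% remission in both arms and 15% v 30% loss: 0.40 x 0.85 = 0.34 and 0.40 x 0.70 = 0.28. The difference is 6 points and the odds ratio is (0.34/0.66)/(0.28/0.72) = 1.32. At 10% v 35% the rates are 0.36 and 0.26, odds ratio 1.60.

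False difference in percentage points, then type I error. Each split averages 22.5%:

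| True remission, both arms | 22.5% v 22.5% | 20% v 25% | 15% v 30% | 10% v 35% |
|---|---|---|---|---|
| 30% | 0; 5.1% | 1.5; 5.7% | 4.5; 10.5% | 7.5; 20.5% |
| 40% | 0; 5.1% | 2.0; 6.0% | 6.0; 13.2% | 10.0; 28.1% |
| 50% | 0; 4.8% | 2.5; 6.0% | 7.5; 15.9% | 12.5; 36.2% |
| 60% | 0; 4.7% | 3.0; 6.4% | 9.0; 20.1% | 15.0; 47.0% |
| 70% | 0; 4.7% | 3.5; 6.9% | 10.5; 25.8% | 17.5; 59.8% |

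The table puts all loss before T2. In simulations with 50% remission and only half the loss that early, the error was 8.1 to 9.1% at 15% v 30% and 14.5 to 18.7% at 10% v 35%.

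**Step 2. Loss between T2 and T3, no true effect.** Carried-forward rate at T3 = T3 rate x (1 - dropout) + T2 rate x dropout. If remission is stable the bias is zero. If remission falls from 60% to 40% and loss is 35% v 10%: 0.40 x 0.65 + 0.60 x 0.35 = 0.47 against 0.40 x 0.90 + 0.60 x 0.10 = 0.42. The arm that loses more gains 5 points; type I error is 9.3%.

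**Step 3. True effect, 57.3% v 30% (odds ratio 3.1), loss before T2.**
- Equal 25% loss: 0.573 x 0.75 = 0.430 v 0.30 x 0.75 = 0.225, odds ratio 2.6. Power is 80%, against 87% with the 60 per arm observed.
- 30% loss in BEST MOOD v 15% in PAST: 0.401 v 0.255, odds ratio 2.0, power 51%.

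**Step 4. Observed data instead.** Simulated null scenarios with 50% remission at T3 and data missing at random gave rejection rates of 4.8 to 5.8% for a likelihood analysis without carry-forward, including 15% v 30% and 10% v 35% loss. This holds only under that assumption. Suppose instead true remission is 40% in both arms, loss is 30% in PAST v 15% in BEST MOOD, and dropouts remit at 10%:
- Carried forward: false difference 0.10 x 0.15 = 1.5 points.
- Observed only: PAST (0.40 - 0.30 x 0.10)/0.70 = 52.9%; BEST MOOD (0.40 - 0.15 x 0.10)/0.85 = 45.3%. False difference 7.6 points, in the opposite direction.

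In this setting the two biases are equal in size when dropouts remit at about 25%; below that, carrying forward is the less biased.

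**The case against.** The strongest reply is that the large error rates need splits such as 15% v 30%, which the article does not give. At 20% v 25% the error is 6 to 7%, and with equal loss it is nominal. That stands: the larger figures are stress scenarios.

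A reader might infer that unequal loss is predicted because the article hypothesises greater treatment engagement in BEST MOOD. The text does not support that step. The hypothesis concerns engagement reported by the youth, whereas the primary outcome is a telephone interview, reimbursed by voucher together with the questionnaire at each time point, which a youth can complete without attending the group. Both arms run eight weekly two-hour sessions and invite youth from the fifth, and the Discussion says that offering equivalent groups reduced the problem of families breaking randomisation. Unequal loss is possible, not forecast.

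A second reply is that *conservative* describes the individual score, since a youth lost early is assumed not to have improved. That is fair for loss before T2, but not for a youth who relapses after T2, and a cautious score for each person does not make a cautious comparison of arms. It is also true that with equal early loss, or more early loss in BEST MOOD, the rule works against BEST MOOD.

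Third, the mixed model is no cure by itself. Youth lost before T2 share the same baseline status, so it is close to a completer analysis for them unless covariates explain dropout, and Step 4 shows that it can be the more biased of the two. This stands and shapes the fix.

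The article also plans to compare dropouts with those retained and has a parent-proxy interview meant to mitigate missing data. Neither alters the carried-forward estimate: the comparison only describes, and the proxy is not named as a substitute for a missing primary outcome.

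**Conclusion.** The stated property is wrong as a general claim. Carrying forward is conservative for the comparison in some cases, such as equal early loss, and anti-conservative in others, such as more early loss in PAST, or more late loss with relapse in BEST MOOD. The bias is conditional on unequal loss (on early loss, also on some of those lost remitting; on late loss, on remission changing after T2). Over 30 to 70% remission and under the assumptions listed, the type I error is about nominal with equal loss, 6 to 7% at 20% v 25%, 10.5 to 25.8% at 15% v 30%, and 20.5 to 59.8% at 10% v 35%. Equal 25% loss shrinks an odds ratio of 3.1 to 2.6.

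A reader might conclude that the trial will produce a false treatment effect, or that its result will reflect who stays rather than who recovers. The article does not support this, because it gives no dropout by arm and no remission rate among those lost. That copied values are treated as observed is a sound objection in principle, but its effect on standard errors was not quantified here. The point should be fixed before outcomes are analysed; it does not undermine the design.

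**What to change.** 1. Remove last observation carried forward, and the word *conservative*, from the primary analysis.
2. Fit the planned mixed model to all observed T2 and T3 data from all randomised families, analysed as randomised, under missing-at-random. Bring in baseline predictors of dropout as covariates or through multiple imputation.
3. Prespecify missing-not-at-random sensitivity analyses: one counting missing as not remitted, and others in which the assumed remission among those lost varies by arm.
4. Report dropout by arm and by time point, so that readers can see which scenario applies.

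The cost is a change of wording and a small amount of extra analysis, with no new data collection. The primary estimate then relies on missing-at-random, so the sensitivity analyses in item 3 are a necessary part of the change.
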